The Philippines study used outcome measures relating to gross motor skills, fine motor skills, expressive language, receptive language, cognitive skills, self-help and social-emotional development, and reported mostly positive impacts in the range of 0.3 to 1.1 standard deviations [32]. Using these impacts as the minimum detectable effect sizes for the Indonesian study, the minimum number of villages to sample was in the range of 7 to 116 villages, depending on the chosen outcome measure, with half of this sample to be allocated to the treatment group and half to the control. We calculated the minimum number of clusters on the basis of a power of 0.9, with an estimated intracluster correlation coefficient (ICC) of 0.23 and with the requirement of ten children surveyed per village. The Philippines study, however, reported unusually high effect sizes especially when compared to a review (published after the sampling for this study) by Nores and Barnett [33], which suggested an average effect size of 0.255 standard deviations for studies investigating the impact of cash transfers, nutritional, educational or mixed interventions conducted in low and middle income countries. Using this as the minimum detectable effect, keeping all else constant, the minimum number of villages required increases to 182. The study eventually sampled 200 villages randomized into treatment and control groups. The power calculations suggest that this would be more than sufficient to detect impact estimates in similar size to those that are reported for the Philippine ECED intervention, and just sufficient to detect the average effects reported in Nores and Barnett’s review.

The size of the matched control group was set equal to the treatment group. In the analysis, we will also be able to present estimates of the impact that rely on standard difference in difference assumptions, comparing the treatment group with the matched control group. The sample size calculations as discussed above are valid under these assumptions; hence the same sample size for the matched control group.

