The first steps in the analysis will be to further validate the instruments used. This will be undertaken by assessing floor and ceiling effects, correlates between measurements, and investigating gradients with socio-economic indicators as well as with age and gender. These analyses will also provide a unique snapshot of the early development of a large cohort of Indonesian children [40].

Having two control groups, an experimental and a matched control, is an unusual feature of this evaluation. Usually an experimental design would be the first choice, and the entire sample would be allocated to this. This rule of thumb was not followed for this evaluation because the effect of the intervention is expected to depend on the duration of exposure to the project. The largest measurable impact is thus expected for children that live in Batch 1 villages at the end of the project. Measuring this impact is the main objective of the evaluation. The randomized control sample is of limited value in estimating this impact as it will have already received the intervention by the end of the project. The matched control sample, on the other hand, will never receive the intervention. Using the observations from the Batch 1 villages and matched control villages, the impact of the project can be estimated using:

(1)$$Y_{\mathrm{ijt}}=\alpha_{t}+X_{\mathrm{ij}0}\beta_{t}+\delta_{t}T_{j}+\epsilon_{\mathrm{ijt}}$$

Where *i* denotes the child, *j* the village, and *t* = 1,2 indicates the time of the baseline, midline and endline surveys. *X* is a vector of village and child baseline characteristics, and *T* indicates whether the village received the project (*T* = 1 for Batch 1 villages and *T* = 0 for matched control villages).

This estimate is a valid impact estimate under the assumption that the outcomes at endline, given baseline characteristics, would be equally distributed in the Batch 1 villages and matched control villages in the absence of the intervention. This assumption cannot be tested at baseline but can be tested at midline. At midline, the averages observed in the randomized control sample of Batch 3 villages are a valid estimate of the expected outcomes in Batch 1 villages in the absence of the intervention. Whether these estimates are equal to those of the matched control sample can be tested by estimating:

(2)$$Y_{\mathrm{ij}1}=\gamma +X_{\mathrm{ij}0}\theta +\mathrm{\pi M}C_{j}+\epsilon_{\mathrm{ij}}$$

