An estimate of *π* that is not significantly different indicates that the matched control sample would have been a valid control group at midline when using the sample of matched control (*MC* = 1) and randomized control villages (*MC* = 0). If this is true, it also increases the ‘comfort factor’ of making this assumption at endline. If not, it provides an indication of the direction in which the estimates from (1) will be biased.

At midline, the experimental design makes it possible to estimate the average treatment effect of the first 18 months of intervention with minimal assumptions. Batch 3 villages will still be a valid control group. Using data from Batch 1 (*T* = 1) and Batch 3 (*T* = 0), the average treatment effect can be estimated by:

(3)$$Y_{\mathrm{ij}1}=\rho +X_{\mathrm{ij}0}\varphi +\vartheta T_{j}+\epsilon_{\mathrm{ij}}$$

Outcomes will be indicators of child development and utilization of early childhood development services. The latter is of interest as the projects aims to increase child development through improved access to early childhood development services. Considering both types of outcome variables provides an opportunity to evaluate the pathways of impact.

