#### Deviations from planned design and consequences for analysis

As mentioned earlier, one deviation from the research design was that the randomized assignment to Batches 1 and 3 was not adhered to. This happened in our case for 20 out of 310 villages. Because this misallocation occurred in relatively few villages, these can be accommodated by using an instrumental variable (IV) estimator in (3). In this case, *T*_*j*_ in (3) is replaced with the actual batch, or the time period of the actual intervention at the time of the survey, and is instrumented with *T*_*j*_. A comparison between the non-instrumented estimate and the IV estimate is insightful in this case. To estimate the impact of the entire project at endline using (1), there is only the non-experimental estimator available. The deviation between the non-instrumented estimator and the IV estimate will give an indication of the effect of using a non-experimental estimator on the parameter estimate.

Another significant deviation from the research design was that the baseline data collection did not take place before the Batch 1 villages started implementing the project. The baseline data collection took place on average 6 months after Batch 1 villages started implementation. Further, the midline data collection took place an average of 9 months after Batch 3 villages started implementation. The delays were a result of the MoNE’s prolonged procurement process to engage the survey fieldwork company and a desire to dispense the funds to the communities. Given these timing issues, in order to assess the impact of the project we will construct measures of dosage, such as months the project was active in a given village.

The consequence of the late baseline survey is that the pre-intervention values cannot be observed from the baseline data for Batch 1 villages. For Batch 3 villages, the intervention had not occurred at the time of the baseline. This is particularly problematic for pre-intervention levels of outcome variables, which in equations (1), (2) and (3) would normally be included in *X*_*ij*0_. With a late baseline, these outcome variables could already have been influenced by the intervention, thus leading to correlation between *X*_*ij*0_ and *T*_*j*_, also in the experimental design.

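### A non-significant π in equation (2) is read as a sign that the matched controls are valid, but the test often misses a bias of half the 0.255 SD review effect

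*Protocol article*

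**What the plan says.** In Planned analyses, the protocol says of the Batch 1 effect at project end: "Measuring this impact is the main objective of the evaluation". Equation (1) estimates it against the matched controls, and the section on deviations from the planned design confirms that at endline "there is only the non-experimental estimator available".

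Equation (1) assumes that, given baseline characteristics X, Batch 1 and matched control villages would have had the same outcomes without the project. The protocol proposes to examine this at midline, taking Batch 3 as the untreated reference: "Whether these estimates are equal to those of the matched control sample can be tested by estimating" equation (2), where π is the coefficient for matched control status. An estimate of π "that is not significantly different indicates that the matched control sample would have been a valid control group at midline". The text continues: "If this is true, it also increases the ‘comfort factor’ of making this assumption at endline". For a significant π: "If not, it provides an indication of the direction in which the estimates from (1) will be biased".

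**The concern.** The sentence turns a failure to reject into positive support. A non-significant π can mean that the groups are alike, or that the comparison is too imprecise to show how they differ. The π comparison has about as many villages as the comparison meant to detect the project's effect, so it cannot rule out biases that are a sizeable fraction of that effect.

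At stake is how the main result is read. District officials chose the matched villages, and some were changed later. Whatever imbalance remains after adjustment for X enters δ in equation (1). A reader told that π supports the controls would give δ more credit than the check can earn. This holds even if Batch 3 had been untouched at midline; its exposure adds a second difficulty.

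**Working it through.** **Inputs from the protocol.** Sample size calculation: ICC 0.23, ten children per village, power 0.9, review effect 0.255 SD, Philippine effects 0.3 to 1.1 SD. Sampling procedures: 90 matched control and 100 Batch 3 villages, 20 households per village. **Assumed:** two-sided 5% (no alpha is stated) and, in the base case, no gain from X.

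**The plan's own figure.** Total villages = 4 × (1.96 + 1.2816)² × [ICC + (1 − ICC)/m] / d². With m = 10 and d = 0.255: 4 × 10.51 × 0.307 / 0.0650 ≈ 198, so about 199 to 201 after rounding or a t correction. The protocol states 182, which I could not reproduce from its inputs. That is a separate matter, and the SE implied by 182 is carried below as a check.

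**Precision of π.** Variance of a village mean: v = ICC + (1 − ICC)/m, which is 0.307 (m = 10) or 0.2685 (m = 20). SE(π) = √[v(1/90 + 1/100)]:
- m = 10: √(0.307 × 0.02111) = 0.0805 SD; 95% half-width 1.96 × 0.0805 = 0.158 SD.
- m = 20: √(0.2685 × 0.02111) = 0.0753 SD; 95% half-width 0.148 SD.

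The test reaches 80% power only for a bias of 2.80 × SE, which is 0.226 or 0.211 SD.

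**Miss rate** = 1 − [Φ(b/SE − 1.96) + Φ(−b/SE − 1.96)]. For b = 0.1275 and m = 10, b/SE = 1.584, so power is Φ(−0.376) + Φ(−3.544) = 0.354.

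| Residual bias b | m = 10 | m = 20 |
|---|---|---|
| 0.1275 SD (half of 0.255) | 64.6% | 60.5% |
| 0.15 SD (half of 0.3) | 53.8% | 48.7% |
| 0.255 SD | 11.4% | 7.7% |
| 0.55 SD (half of 1.1) | about 0 | about 0 |

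**Sensitivity at b = 0.1275 SD** (m = 10, then m = 20, where two values are given):
- SE implied by the stated 182 villages, rescaled to 90 v 100 (0.0771): 62.0%.
- ICC 0.10: 48%, 37%. ICC 0.05: 37%, 20%. ICC 0.30: 70%, 67%.
- X explains 30% of variance: 53%, 47%. X explains 50%: 39%, 33%.
- Two-sided 10% test: 52%, 48%.

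**What π measures.** Let s be the difference, matched controls minus project villages, that would exist without the project. Let e be the effect of Batch 3's roughly 9 months of exposure at midline, reported in the section on deviations. Then π estimates s − e, while δ estimates (full effect − s), taking s as constant over time. If s equals e, π is zero although the controls are not comparable. Correcting δ by adding π gives (full effect − s) + (s − e) = full effect − e, which removes real project effect.

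**The case against.** **The wording is soft and nothing is gated.** This stands. A reader might infer that the plan certifies the controls or makes equation (1) conditional on π. It does neither: equation (1) is reported whatever π shows, and the Discussion names the threat to internal validity as the matched group's main disadvantage. The error is in how a non-significant π is to be read.

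**0.255 SD is not the design effect.** This also stands. A reader might infer that the trial was sized on it. The protocol sized on a Philippine study that "reported mostly positive impacts in the range of 0.3 to 1.1 standard deviations". The review that "suggested an average effect size of 0.255 standard deviations" appeared after sampling and served as a later check. Half of 0.255 SD is therefore a benchmark chosen here. It is a reasonable one, because the protocol itself calls the Philippine effects unusually high.

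**Covariates will sharpen π.** Partly right. Equation (2) includes X, and for Batch 3 the baseline preceded the project. But π checks equation (1)'s assumption only if both use the same X, and the protocol says baseline outcomes in Batch 1 may already be affected. Even at an assumed 50% of variance explained, a third or more of such biases are missed.

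**The plan has other safeguards.** It mentions difference-in-difference estimates and an IV v non-instrumented comparison. The first is weakened by the late baseline. The second concerns departures from batch assignment, not the officials' choice of matched villages.

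**The rule does not create the false positives.** Correct. A reader might infer that screening on π inflates endline error. With an assumed bias of 0.1275 SD and no project effect, simulation finds equation (1) significant in 23-40% of outcomes with a non-significant π. Without any screen the figure is 35-40%. The error comes from the bias; the check leaves it unchanged or somewhat lower. The harm is false reassurance.

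**Conclusion.** The concern holds as a flaw of interpretation in the text supporting the main estimate. On the protocol's inputs, an assumed two-sided 5% test and no covariate gain, a non-significant π is compatible with residual biases of roughly 0.15 SD or more, and a bias of 0.1275 SD is missed 60-65% of the time. The figure depends on the assumptions: 49-54% for half of 0.3 SD, 37-48% at ICC 0.10, 33-53% with 30-50% of variance explained, and near zero for half of the largest Philippine effects.

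Large biases are not hidden: one of 0.255 SD is detected 89-92% of the time. Nor does every imbalance reach δ; only what remains after X does. The documents do not show that the matched controls are in fact biased, only that this check cannot establish that they are not. Batch 3's exposure means that even a precise π would not isolate matching bias.

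**What to change.** 1. Delete the statement that a non-significant π indicates validity, and the added support at endline drawn from it.
2. For each listed outcome, report π with its cluster-robust 95% interval, described as the range of selection bias not excluded.
3. For each endline δ, report the residual bias after X that would remove its significance, |δ| − 1.96 × SE(δ), and compare it with that range. For example, with SE 0.0805 at endline, a δ of 0.255 SD loses significance at a bias of 0.255 − 0.158 = 0.097 SD, which lies inside ±0.158 SD even if π is estimated as zero.
4. Describe effects that do not survive the comparison as inconclusive on selection.
5. State that π mixes matching bias with a partial treatment effect from Batch 3's roughly 9 months of exposure, so step 3 is a sensitivity analysis.

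Do not substitute an equivalence gate. With a margin of 0.1275 SD, the 90% half-width is 1.645 × 0.0805 = 0.132 SD at m = 10, so the interval can never fit. At m = 20 it fits about 4% of the time with zero true bias. For the reason shown in the working, do not correct δ by π either.

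The cost is a change of wording and some extra reporting from estimates already planned, with no new data. The downside is that some endline conclusions become more cautious.

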#### Differential treatment effects

We will report results for the following sub-groups: boys/girls, poor/rich (defined on the basis of an asset index with poor being defined as those who are in the bottom half) and enrolment in ECED services before commencement of the project. All sub-groups will be defined on the basis of information collected in the baseline data.

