In addition to the program delivery, the sector investment loan included funds for monitoring, supervision and evaluation of the program to be undertaken jointly with the Ministry of National Education (MoNE) and the World Bank. One primary facet of this agreement was an impact evaluation with the goal of understanding whether the project improves children’s development and readiness for primary school, and what factors (for example, community cohesion, remoteness and parents’ socio-economic status) contribute to the effectiveness of ECED services.

This paper documents the study protocol for this evaluation consistent with the guidelines for the reporting of a randomized controlled trial (RCT) and, in particular, the extension of the Consolidated Standards of Reporting Trials (CONSORT) statement for cluster randomized trials [29] and pragmatic RCTs as advised by Zwarenstein *et al*. [30].

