#### Instrument development and piloting

Access to services, service utilization, asset inventory, dwelling attributes and consumption history by the household were collected using a series of questions that were previously constructed for the Indonesian Family Life Survey (IFLS), a renowned panel study focusing on demographic, poverty and health measures. The child and caregiver questionnaires include several internationally-recognized standard scale instruments and anthropometric measures. We also collected information about the child’s development and health history from the parent/caregiver. None of the standard tools used to measure childhood development had been applied in Indonesia before. As such, the instruments had to be translated and adapted to the Indonesian culture and circumstances, and the study design meant that some of the standard measures of child development needed to be amended.

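### Differential effect by wealth is examined only through a median split of the asset index; an interaction with the full index would usually use the data better, at almost no cost

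*Protocol article*

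**What the plan says.** Under Differential treatment effects the protocol announces "We will report results for the following sub-groups" and lists sex, wealth and prior enrolment in ECED services. The wealth groups are "poor/rich (defined on the basis of an asset index with poor being defined as those who are in the bottom half". The same section adds: "All sub-groups will be defined on the basis of information collected in the baseline data".

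The background section on the ECED program gives, as part of the impact evaluation's goal, to understand "what factors (for example, community cohesion, remoteness and parents’ socio-economic status) contribute to the effectiveness of ECED services".

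The raw material for the index is described under Instrument development and piloting: "Access to services, service utilization, asset inventory, dwelling attributes and consumption history by the household were collected". How the index is built, its scale and its distribution are not given. The protocol names no interaction test, no expected size of effect modification and no power for any subgroup. Its power statement concerns the main effect only.

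**The concern.** Whether the effect varies with wealth is a declared question, and the program is aimed at poor families. The one stated analysis reduces a graded measure to two halves. A household just below the median then counts the same as the poorest, and one just above it the same as the best off. If the effect changes gradually along the index, this discards information that has already been collected, and a real gradient is more likely to be missed. Effect modification is hard to detect in any case. The Discussion already warns that showing an impact might be difficult, with about 11 months of differential exposure between Batch 1 and Batch 3 at midline.

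**Working it through.** **Plan's own figure.** There is none for the wealth subgroup. The nearest is 182 villages for a main effect of 0.255 SD, "on the basis of a power of 0.9" and "with an estimated intracluster correlation coefficient (ICC) of 0.23", with ten children per village. The usual formula, 2 × 2(1.96 + 1.2816)²/0.255² × (1 + 9 × 0.23)/10, gives about 198 at two-sided 5%. Alpha and sidedness are not stated, and nothing below depends on this figure.

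**Inputs from the protocol.** 200 randomised villages, 1:1; ICC 0.23; 10 children per village (Sample size calculation) or 20 households per village (Sampling procedures).

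**Assumed inputs.** Normal index; linear gradient; outcome SD 1; two-sided 5% test; gap in effect between the two halves of 0.05 to 0.20 SD; share of index variance between villages of 0 or 0.30.

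**Step 1, information kept, no village clustering of the index.** This is the squared correlation between a normal variable and its median split: 2/π = 0.637. The loss is 36%, equal to needing π/2 = 1.57 times the sample. Other shapes keep 75% (uniform), 65% (10-item count), 52% to 59% (moderately skewed) and 48% (exponential).

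**Step 2, information kept within villages, village share s = 0.30.** (1 − s)(2/π) / [1 − (2/π)·arcsin(s)] = 0.70 × 0.637 / (1 − 0.194) = 0.553, so about 45% is lost.

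**Step 3, largest power loss, no clustering.** Power = Φ(λ − 1.96), and the split multiplies λ by √0.637 = 0.798. With 80% power from the continuous index, λ = 1.96 + 0.84 = 2.80; the split has 2.80 × 0.798 = 2.24, giving Φ(0.28) = 61%, a loss of 19 points. Over all starting powers the maximum is 19.4. The loss is 9 points from 30%, 17 from 90% and 6 from 99%.

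**Step 4, power in this design.** Without clustering, the SE of a balanced 2×2 interaction is √(16 × 0.77/N): 0.0785 for N = 2,000 and 0.0555 for N = 4,000. For a 0.15 SD gap and N = 4,000, the split has λ = 0.15/0.0555 = 2.70, power 77%; the continuous index has λ = 2.70/0.798 = 3.39, power 92%. The columns for share 0.30 come from simulation (1,500 replicates, random-intercept GLS), except the 0.05 row, which halves the λ values behind the 0.10 row.

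Power, continuous v split (%):

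| Gap (SD) | 10 children, share 0 | 20 children, share 0 | 10 children, share 0.30 | 20 children, share 0.30 |
|---|---|---|---|---|
| 0.05 | 12 v 9 | 20 v 14 | 10 v 8 | 15 v 11 |
| 0.10 | 36 v 25 | 62 v 44 | 27 v 18 | 46 v 30 |
| 0.15 | 67 v 48 | 92 v 77 | 53 v 34 | 82 v 56 |
| 0.20 | 89 v 72 | 99.5 v 95 | 76 v 54 | 96 v 81 |

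The 26-point loss in the last column agrees with step 2: λ = 1.96 + 0.915 = 2.88 at 82%, times √0.553 = 2.14, giving Φ(0.18) = 57%, a loss of 25 points. At the large end, a gradient of 0.15 SD per index SD (a gap of 0.15 × 1.596 = 0.24 SD) with 20 children and no clustering loses 0.9 points.

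**Step 5, the reverse case.** If the effect is a step exactly at the median, the continuous term keeps only 2/π of the split's information. For a 0.15 SD step, N = 4,000 and no clustering, the split has 77% power and the linear term has λ = 2.70 × 0.798 = 2.16, power 58%.

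**The case against.** The strongest reply is that nothing here is an error. A poor/rich contrast fixed in advance is a legitimate display, the effect among the poorer half is of policy interest in its own right, and a cut defined beforehand fits the protocol's wish to limit false positives. The section promises results by subgroup; it names no test, claims no subgroup power and does not rule out a continuous interaction in a fuller plan that is not shown. Nor is it the complete analysis of the stated goal, since community cohesion and remoteness are named there and are not among the subgroups. All of this stands, and it limits the point to efficiency. It does not remove the fact that the one stated treatment of wealth is a dichotomy.

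The objection to the size also stands in part. Gaps of 0.10 to 0.20 SD are 39% to 78% of the 0.255 SD main effect, and the protocol gives no ground for expecting modification that large. The 20 children per village span two age cohorts, so outcomes analysed in one cohort have about 10. That the index is effectively continuous is an inference from its being built on an asset inventory and cut into halves.

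A reader might infer that the split costs this trial a definite 9 to 26 points of power. The documents do not support that: they give no gradient, index distribution or village share. The upper end belongs to a clustered index, for which the information loss is nearer 45% than a third. A reader might also fault the cut for depending on this sample, or the word rich for describing households in poor villages. The first applies equally to a standardised index and its percentiles; the second changes no result.

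**Conclusion.** The point holds as a minor efficiency improvement to a secondary analysis. Given a roughly normal, continuous index and a roughly linear gradient, the median split keeps about 64% of the information on effect modification by wealth, and about 55% if 30% of index variance lies between villages. The resulting power loss is conditional: a few points or less for very small or very large gradients, at most about 19 points for an unclustered normal index, and about 26 points in the one scenario of village share 0.30, 20 children and a 0.15 SD gap. It would be wrong to conclude that the subgroup analysis is invalid, that the protocol contradicts itself, or that any primary estimate is affected.

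**What to change.** In Differential treatment effects, state that differential effect by wealth is assessed by the interaction of treatment with the continuous baseline asset index. Add the index and its product with treatment to equations (1) and (3), report estimated effects at chosen percentiles (for example the 25th and 75th), and add a quadratic term as a check on linearity. Keep the bottom-half/top-half table as a descriptive display.

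The cost is about one sentence and one further model term (plus the quadratic check), with no new data. Where (3) is fitted with the instrumental-variable estimator, the product term needs its own instrument, assigned batch times the index. The real downside is the linearity assumption: if the effect changes as a step at the median, the split is the more powerful test, which is another reason to keep the table.
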